#### MEDITERRANEAN DIET: GENERAL RECOMMENDATIONS

| FOOD                                                                              | GOAL                                   |
|-----------------------------------------------------------------------------------|----------------------------------------|
| RECOMMENDATION                                                                    |                                        |
| 1. Olive oil (extra virgin if possible)                                           | Main culinary fat or $\geq 4$ tbsp/day |
| 2. Tree nuts and peanuts (peanut butter without added sugars or hydrogenated fat) | $\geq 3$ servings/wk                   |
| 3. Fresh fruit                                                                    | $\geq 3$ servings/day                  |
| 4. Vegetables                                                                     | $\geq 2$ servings/day                  |
| 5. Fish (including fatty fish) and seafood                                        | $\geq 3$ servings/wk                   |
| 6. Legumes (chickpeas, beans, lentils)                                            | $\geq 3$ servings/wk                   |
| 7. Sofrito a                                                           | $\geq 2$ servings/wk                   |
| 8. Fresh Herbs, Allium (onion, garlic, etc)                                       | $\geq 2$ servings/day                  |
| 9. Yogurt                                                                         | $\leq 2$ servings/day                  |

|                                                                         |                                       |
|-------------------------------------------------------------------------|---------------------------------------|
| 10. White meat                                                          | Instead of red meat (2-3 servings/wk) |
| 11. Whole grains/cereals b                                   | Instead of refined grains             |
| 12. Wine with meals (optional, only for habitual drinkers) c | ≥7 glasses/wk                         |
| DISCOURAGE                                                       |                                       |
| 13. Soda drinks (encourage water as a beverage)                         | <1 drink/day                          |
| 14. Spread fats                                                         | <1 serving/day                        |
| 15. Red and processed meats                                             | <1 serving/day (< 2 servings/wk)      |
| 16. Commercial bakery foods sweets, and pastries d           | <3 servings/wk                        |
| 17. Fast food                                                           | ≤1/wk                                 |

a Sofrito is a tomato-sauce made with onion and garlic, slowly simmered with olive oil

b Women 75 g/day, men 90 g/day or ≥5 servings/day. Whole grains brown rice, whole grain bread and pasta. c Optional and only for habitual drinkers without alcohol-related health problems

d Homemade sweets are preferable to store-bought or commercially-produced sweets

Peer-education and support: In addition, we will identify volunteers among consented participants at each fire house assigned to the nutrition intervention to become station “champions”. These peer-nutrition leaders can help to motivate their colleagues and also report back to the investigators regarding which strategies are most successful as well as on obstacles encountered.

**Discounted food access:** Among the most important perceived barriers to healthy eating are the time and cost of shopping. Therefore, we have partnered with Kroger supermarkets, a large national chain with numerous stores in the Indianapolis area, to provide discounted access to key Mediterranean foods (eg extra-virgin olive oil, nuts, fruits, vegetables, legumes, whole-unrefined grains, and lean proteins) for both participating firefighters and their families. The discount program within the study will utilize Kroger’s existing shopper loyalty program which constantly features discounted items and promotions for registered customers. All participating firefighters will be encouraged to register with the program if not already members. On a regular periodic basis (e.g. 1-2 times per month), Kroger staff will identify and “package” existing store discounts, price promotions and coupons that are consistent with the Mediterranean Diet intervention into “mailers” which advertise and list the items and promotions. Copies of the mailers will be sent to the firehouses assigned to the active intervention. In this way, both firefighters and their families may be aware of the discounts and have the option to use them.

Kroger staff will use the following guidelines to select food items related to those highlighted in green here for inclusion in the mailers.

**TABLE 1.** General Dietary Recommendations Based on Mediterranean Diet Principles

| Daily Intake                             |                                          | Weekly Intake          |               | Sparing Intake                                              |               |
|------------------------------------------|------------------------------------------|------------------------|---------------|-------------------------------------------------------------|---------------|
| Food Item                                | Goal                                     | Food Item              | Goal          | Food Item                                                   | Goal          |
| Olive oil                                | ≥4 tbsp/day                              | Nuts                   | 3–7 serv/week | Red and processed meat                                      | ≤2 serv/week  |
| Yogurt                                   | ≤2 serv/day                              | Fish/seafood           | ≥3 serv/week  | Commercial sweets and refined carbohydrates §,   | ≤3 serv/ week |
| Fresh fruits                             | ≥3 serv/day                              | Eggs                   | 2–3 serv/week | Soda and sugary drinks §,                        | <1/day        |
| Vegetables                               | ≥3 serv/day                              | Poultry                | 2–3 serv/week |                                                             |               |
| Whole and refined grains*                | Women 75 g/day,
men 90 g/day          | Legumes                | ≥3 serv/week  |                                                             |               |
| Fresh Herbs, Allium (onion, garlic, etc) | ≥twice/day                               | “Sofrito” ‡ | ≥2 serv/week  |                                                             |               |
| Wine with meals †             | Men 1–2 glasses/day
Women 1 glass/day |                        |               |                                                             |               |

\*Whole grains brown rice, popcorn, and any grain food with a carbohydrate to fiber ratio no more than 10:1.

†Optional and only for habitual drinkers without alcohol-related health problems.

‡Sofrito is a sauce made with tomato and onion and/or garlic, slowly simmered with olive oil.

§Homemade sweets are preferable to store-bought or commercially-produced sweets.

||Discouraged.

JOEM • Volume 58, Number 3, March 2016

Participants may also have access to additional discounted food options during the course of the study as follows:

1. Discount coupons obtained directly from producers which can be redeemed at Kroger and other local stores. For example, Barilla pasta has pledged its support to provide coupons for “Barilla Plus”, a line of pastas which combine ALA-3- enriched whole grain and legume flours to produce a high fiber, higher protein product yielding delicious pasta that is more nutritious and promotes better glucose metabolism than typical pasta from refined flours.

2. “Starter” supplies of extra-virgin olive oil, avocados and nuts and for fire house kitchens at no cost, along with coupons and options for obtaining additional product at discounted prices directly through food companies partnering with the study.

3. Encourage and facilitate access to farmer’s markets and produce from local community gardens within the City of Indianapolis and surrounding area.

According to each participant’s preference, they may sign up for either email or text message encouragement and reminders during the intervention. For those opting in to this option, they will receive brief text or email messages 2-4 times per week reinforcing the healthy dietary and lifestyle principles as discussed above.

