## PHASE I (first 12 months of the study) Group 2: No

### intervention.

#### **Mediterranean Diet Nutritional Intervention for 12 Months for Group 1.**

The extent to which consented participants personally engage in the MDNIs is voluntary, and the additional time commitment required for the study is nominal. The Mediterranean Diet intervention will include educational materials; opportunities for discounted access to healthy foods consistent with the Mediterranean diet (e.g. extra-virgin olive oil, nuts, fruits, vegetables, legumes, whole-unrefined grains, and lean proteins) for both participating firefighters and their families; peer education/support, on-line learning, and email and text message encouragement and reminders. Each of these pieces of the intervention is explained in further detail below.

Educational materials (online learning) will be provided via the study website; group educational sessions and written materials. Examples of our educational information include: a brochure with Mediterranean Diet recommendations, shopping list recommendations and sample recipes, tips to practice the Mediterranean Diet at both home and work and a firefighter-specific Mediterranean Diet Pyramid have been developed for this purpose. These materials may be supplemented as the study progresses to include additional modified Mediterranean Diet recipes based on the firefighters' and their families' preferences and requests (e.g. supply a modified recipe for healthy Mediterranean lasagna or chili based on a fire station's request); short videos; and links to other healthy eating materials. The videos may include: cooking demonstrations; talks with firefighter "champions" (brief interviews and commentaries from firefighters who are successfully practicing the Mediterranean diet) and similar content.

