The initial and periodic group educational sessions with larger groups (up to 100 firefighters) will be led by the Harvard investigators and the local medical team (Public Safety Medical) and held in fire department classrooms. These will be followed-up by more frequent, smaller group (5-20 firefighters) diet and fitness sessions in fire house classrooms and kitchens by our Indiana-based dietitian and Health/Fitness Specialist, [name]. [name] is contracted with PSM and has a long experience working with firefighters. The sessions may include: didactic presentations, interactive discussions and cooking demonstrations that follow the general recommendations (see below).

Specific topics that we plan to address in the group educational sessions include:

1. Basic Mediterranean Diet principles;
2. The benefits of Olive oil and nuts and how to introduce them into the diet;
3. Overcoming Challenges while following a Mediterranean Diet;
4. How to plan a weekly menu and shopping list;
5. How to choose wisely when eating out (restaurants/parties);
6. Making smart choices regarding "Fast food".

We may also provide in-person chef-led, Mediterranean cooking demonstrations at fire stations in the intervention group. Some of the general educational sessions and cooking demonstrations may be videotaped or otherwise adapted for internet accessibility on the study website.

All of the educational sessions and materials will be centered on the principles and general recommendations outlined in the table below.

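### The wine goal in the table that governs all the education is a floor of 7 glasses a week with no upper limit

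*Protocol*

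**What the plan says.** Protocol section 4.6 describes the 12-month intervention for Group 1 and states: "All of the educational sessions and materials will be centered on the principles and general recommendations outlined in the table below". The table that follows, headed Mediterranean Diet: General Recommendations, has 17 rows: 12 recommended items and 5 discouraged ones. Row 12, in the recommended part, is "12. Wine with meals (optional, only for habitual drinkers) c | ≥7 glasses/wk". Its footnote c reads "Optional and only for habitual drinkers without alcohol-related health problems".

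Later in the same section, Table 1 (General Dietary Recommendations Based on Mediterranean Diet Principles) gives the wine goal as "Men 1–2 glasses/day Women 1 glass/day", with a footnote restricting it to the same people. The sentence that introduces Table 1 is "Kroger staff will use the following guidelines to select food items related to those highlighted in green here for inclusion in the mailers".

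No other part of the protocol shown sets a maximum for wine.

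**The concern.** The column is headed as a goal. Read literally, a habitual drinker who takes the option and drinks fewer than 7 glasses a week falls short of the goal, and no amount is too much. That is an unsuitable form for alcohol.

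Footnote c is the only alcohol safeguard attached to the row, and it governs eligibility for the option, not quantity. The exclusion criteria in section 4.5 contain nothing on alcohol. Phase II delivers the same intervention to the crossed-over groups, and section 7.1 says every consenting firefighter receives it at some point, so the wording applies across the trial. Sections 4.8 and 10 rest the minimal-risk classification on the safety of the diet. The written diet should therefore carry the limit that the protocol already has elsewhere.

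**Working it through.** There is no sample size, power or error-rate figure to reproduce. The check compares the two tables in the same units and then asks whether the wording could be a reading error or simply the table's house style.

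**Weekly amounts.** Table 1 is in glasses per day, so multiply by 7:

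- women: 1 × 7 = 7 glasses/week
- men: 1 × 7 = 7 up to 2 × 7 = 14 glasses/week

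| | Women, per week | Men, per week |
|---|---|---|
| General Recommendations, row 12 | 7 or more, no upper limit | 7 or more, no upper limit |
| Table 1 | 7 | 7–14 |

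The lower ends agree at 7, so the two tables do not formally contradict each other. What is lost is the upper end: 7 for women and 14 for men. For women, Table 1's whole amount becomes the minimum of an open-ended goal. A woman drinking 14 glasses a week meets row 12 while taking 14 / 7 = 2 times the Table 1 amount.

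**Could the sign be misread from the PDF?** Unlikely. The same table prints an at-most sign correctly for yogurt (row 9) and fast food (row 17).

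**Is it house style?** Largely, yes:

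- Recommended rows 1–8 and 12 use an open-ended lower bound: 8 + 1 = 9 of 12. Row 9 is a ceiling, row 10 a range and row 11 a substitution.
- Discouraged rows 13–17 are all ceilings: 5 of 5.
- Ceilings in the whole table: 1 + 5 = 6 of 17.

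Nuts were shortened in the same way: 3 or more servings a week here, against 3–7 in Table 1. This explains how the wine wording probably arose, but it does not make the form suitable for alcohol. The table is able to state a ceiling (row 9). It can also state amounts by sex, since footnote b on whole grains gives "Women 75 g/day, men 90 g/day or ≥5 servings/day". It does neither for wine.

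**The case against.** The strongest reply is that the protocol does give bounded amounts, in the same section and under a title that presents Table 1 as general dietary guidance. The green highlighting that marks the mailer items is lost in the text available, so it cannot be seen whether wine was among them. If it was not, the wine row in Table 1 makes sense only as dietary advice. Staff who hold the protocol can find the limits shortly after the education table.

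The practical safeguards also count. Wine is optional and restricted to existing drinkers without alcohol-related problems. "The extent to which consented participants personally engage in the MDNIs is voluntary". Sessions are led by the investigators, the medical team and a dietitian. None of the six planned topics is alcohol, and wine is not named among the discounted foods or starter supplies. Participants see a brochure, a pyramid and a website, which are not shown and may state a limit. The grain comparison is also loose: footnote b concerns whole grains and includes an open-ended alternative, whereas Table 1's row covers whole and refined grains.

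Most of this stands, and it keeps the point small. Harm to participants is possible but not demonstrated, and the grain footnote shows only that the table can hold sex-specific amounts. None of it supplies a ceiling in the table to which the education is tied. Nothing in the text sends educators to Table 1 for amounts. If the brochure does state a limit, the governing table should match it.

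**Conclusion.** The concern holds, as a minor participant-safety point about how the intervention is specified. The education table keeps Table 1's lower end of 7 glasses a week and drops the upper ends of 7 (women) and 14 (men). It affects only habitual drinkers without alcohol-related health problems who take the option, and the protocol does not give their number. The conclusion about the written text is firm. How far it reaches participants depends on an assumption that cannot be checked here, namely that the unseen materials follow the table as written. No effect on adherence scoring, endpoints, power or analysis is shown.

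**What to change.** In row 12, replace the goal with: optional, habitual drinkers only, up to 1 glass/day (women) or up to 2 glasses/day (men), with meals. Keep footnote c. The figures are the upper ends of the protocol's own Table 1; treating them as maxima is a proposal made here, because Table 1 presents them as goals. Copying Table 1's amounts unchanged (women 7, men 7–14 glasses a week) would also restore the upper end, but would leave a minimum for alcohol in place.

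Then check the brochure, pyramid, website and text or email messages, and use the same wording wherever an amount of wine is given. Table 1 can stay as it is; it carries a journal source line ("JOEM • Volume 58, Number 3, March 2016").

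The cost is one table cell, a check of materials already developed, and a routine amendment, since section 22 requires the IRB to be notified of protocol changes. Visits, sample size and analysis are unaffected.

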## PHASE II

### Mediterranean Diet Nutritional Intervention for 6 months for Groups 2 and 3 (and 4 in the final 6 months).

This intervention will be exactly as described above for Phase I, but will last 6 months. Afterwards, over the final 6 months of the study, the participants from Group 2 in Phase 1 will be encouraged to maintain eating Mediterranean style on their own using the support of the discount program, the study website and the support of fellow firefighters and family.

**Group 2: No intervention.** Over the next 12 months (year two). Phase 1 Group 1 participants will be encouraged to maintain eating Mediterranean style on their own using the support of the discount program, the study website and the support of fellow firefighters and family.

The table below summarizes data collection from all consented firefighter participants across the timeline of the 2-year study. Fishers Department FF will be joined to the study in the 12 months of follow up of the original Feeding America's Bravest

| Questionnaires/Measurements        | Baseline | 6months | 12months | 18months | 24 months |
|------------------------------------|----------|---------|----------|----------|-----------|
| Nutrition/Lifestyle questionnaires | X        | X       | X        | X        | X         |
| Blood Pressure                     | X        | X       | X        | X        | X         |
| Height/Weight                      | X        | X       | X        | X        | X         |
| Waist circumference                | X        | X       | X        | X        | X         |
| Body composition (Tanita)          | X        | X       | X        | X        | X         |
| Medical exam results transfer      | X        |         | X        |          | X         |

: .

The table below summarizes data collection from a random subset of consented firefighter participating in the biomarker study

| Biomarker proposal                                   | Time point1
(Dec2017/Jan 2018) | Time point2
(June2018) |
|------------------------------------------------------|-----------------------------------|---------------------------|
| Blood sample collection (fatty acids measurements)   | X                                 | X                         |
| Urine sample collection (hydroxytyrosol and tyrosol) | X                                 | X                         |
| Stool samples                                        | X                                 | X                         |

**4.7. Does the study involve the collection of data/specimens (including the use of existing data/specimens)?**

☐ No ☒ Yes: If yes; indicate how, when, where and from whom specimens or data will be obtained

Fire department provided annual occupational medicine examinations (part of the firefighters' usual care) will be provided by Public Safety Medical as per existing IFD policies and without regard to study participation. For consented participants **ONLY**, medical exam and biomarkers results will be transferred to the Harvard Chan research team as described above, as coded data in password-protected files. Medical exam data that will be provided to the study team for consented IFD subjects include: at rest and maximal heart rate, systolic and diastolic blood pressure, heart rate recovery, electrocardiographic findings at rest, hip and waist circumference, body composition, data regarding the grip strength, leg-press and push-ups, and routine lab values (e.g. lipid panels, hs-CRP and glucose), biomarkers from blood and urine and microbiome composition from the stools..

**4.8. Is there a data and safety monitoring plan (required for greater than minimal risk studies)?**

☐ No ☒ Yes: If yes; describe the plan

The proposed research presents minimal risk because the Mediterranean diet is proven to be effective and safe. Nonetheless, because our aim is to register our nutritional intervention in order to publish in high-impact journals, a data advisory monitoring board (DAMB) has been selected based on the members' nutrition, clinical, methodologic, statistical, or fire service expertise. The DAMB members include: [name] (Professor in Biostatistics, Research Methods and Epidemiology of Nutrition, at the Department of Nutrition Science - Dietetics, Harokopio University in Athens) who has been a leader in statistics and cardiovascular and nutritional epidemiology; [name] [name] (Senior Principal Investigator, Center for Fire, Rescue & EMS Health Research, Institute for Biobehavioral Health Research, National Development & Research Institutes, Inc.) with extensive experience in statistics, epidemiology and the United States fire service; and [name] (Lecturer in Public Health, Cyprus International Institute for Environmental and Public Health) who is an accomplished epidemiologist and statistician.

The DAMB will monitor interim data (described in Section 4.7) in coordination with our team's statistician ([name] and the study PI, [name]).

**4.9. Are there any anticipated circumstances under which participants will be withdrawn from the research without their consent?**

☒ No ☐ Yes: If yes; describe the circumstances as well any associated procedures to ensure orderly termination

**5. Data/Statistical Analyses Plan****5.1. Briefly describe the plan for data analysis (including the statistical method if applicable)**

Data recording, storage, management, cleaning and basic analyses will be performed using SPSS. The data will be imported into Stata and SAS for more advanced statistical analyses such as multivariable regression

and longitudinal data analysis, as needed. Differences in the mean values of a quantitative variable between two groups will be assessed using the independent t-test whereas differences in mean values among three or more groups will be examined using the analysis of variance (ANOVA) technique (or non-parametric Wilcoxon and Kruskal-Wallis tests, respectively, as appropriate). Differences in qualitative characteristics will be compared using the chi-square test, or Fisher's exact test, or McNemar's test (for paired comparisons), as appropriate. Statistical significance for all analyses will be  $p < 0.05$ , and all tests will be two-tailed.

Phase 1: During the first 12 months of the nutritional intervention, **groups 1 (Mediterranean Diet intervention) and 2 (no intervention) will be compared directly on an intention to treat basis according to the randomization of each participant's fire house.** As several outcomes will be assessed on each participant throughout the study (3 annual medical exams and 5 semi-annual assessments (where weight, mMDS, etc. will be evaluated)), repeated measures techniques, such as mixed modeling and generalized estimating equation models, will be utilized to estimate changes over time on key outcomes. We will take into consideration the specific variance-covariance structure of correlated measurements. After adjusting for baseline and time-dependent covariates, changes in the outcomes of interest will be assessed and compared among groups. We expect our greatest power to be for within-group changes (paired comparisons).

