## 1. Specific Aims

1. Develop a multi-pronged, Mediterranean Diet Nutritional Intervention (MDNI) behavior change strategies including: diet/lifestyle education; discounted access to key Mediterranean diet foods; electronic education platforms and reminders. MDNI components will be refined via surveys, literature review and local/national firefighter input including labor/management and fire service focus groups.

Hypothesis (1). Cost-effective, fire-service MDNIs will be developed for the cluster-randomized, career firefighter diet intervention.

2. Cluster Randomized Diet Intervention-Phase I- the Indianapolis Fire Department (IFD) has over 1,000 members. All 44 IFD firehouses will be cluster randomized into two groups and then individual members will be consented regarding study participation. Group 1 will receive an active 12-month MDNI, while Group 2 will receive no intervention. Firefighters categorized as "Administrative Staff" by the IFD will also be approached for participation and if they consent, be assigned to Group 1 because they are not assigned to specific firehouses.

3. Cluster Randomized Diet Intervention -Phase II: Group 1 will cross-over to "self-sustained continuation" for 12 months to examine persistence of behavior change during this less intense, self-directed maintenance diet intervention. Group 2 will cross-over to receive the MDNI for 6 months (assessing a shorter MDNI), followed by a final 6 months of self-sustained continuation. An additional neighboring fire department, Fisher's (IN), will have its 6 firehouses randomized to receive the MDNI (Group 3) or no intervention (Group 4) for six months, and then individual members will be consented regarding study participation. After 6 months, the 3 stations in the MDNI (Group 3) will cross-over to "self-sustained continuation" for the last 6 months to examine persistence of behavior change during this less intense, self-directed maintenance diet intervention. Group 4 will cross-over to receive the MDNI for 6 months (assessing a shorter MDNI).

4. A similar 12-month Cluster Randomized Diet Intervention in the six fire stations of the Fishers (IN) Fire Department with a cross-over by the control group to intervention after 6 months will also be done.

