**4.2. Indicate the study's duration - and the estimated date of study completion**

2 years. December 2018

**4.3. Indicate the total number of participants (if applicable, distinguish between the number of participants who are expected to be screened and enrolled, and the number of enrolled participants needed)**

1,000 career firefighters (500 assigned to group 1 and 500 assigned to group 2). We will approach as many eligible members as possible to consent at least 500 and up to 1,000 participants maximum. For the biomarkers nested study, a total of up to 100 firefighters, selected at random evenly from the existing study arms in Indianapolis

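### Fire houses are randomised, but section 5.1 tests firefighters as independent individuals and models only within-person correlation, so p-values and confidence intervals will be too optimistic

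*Protocol*

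**What the plan says.** Section 1 makes the fire house the unit of allocation: "All 44 IFD firehouses will be cluster randomized into two groups". In Fishers, the second department, the plan "will have its 6 firehouses randomized to receive the MDNI (Group 3) or no intervention (Group 4) for six months". Section 4.3 aims to "consent at least 500 and up to 1,000 participants maximum".

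Section 5.1 then lists the tests for group differences. For continuous outcomes: "Differences in the mean values of a quantitative variable between two groups will be assessed using the independent t-test", with ANOVA and rank tests as companions. For categorical outcomes: "Differences in qualitative characteristics will be compared using the chi-square test, or Fisher's exact test, or McNemar's test (for paired comparisons), as appropriate". One two-sided 0.05 threshold applies to all analyses, and nothing confines these tests to baseline or descriptive tables.

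For Phase 1 the section adds that "repeated measures techniques, such as mixed modeling and generalized estimating equation models, will be utilized to estimate changes over time on key outcomes". The reason given is that each participant contributes several outcomes over time, through annual examinations and semi-annual assessments. It continues: "We will take into consideration the specific variance-covariance structure of correlated measurements". The fire house appears in section 5.1 only as the rule for assigning participants to groups under intention to treat.

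**The concern.** The effective sample size of a cluster-randomised comparison depends on the number of clusters and on how alike their members are. Much of this intervention works through the station: sessions in fire-house classrooms and kitchens, station champions, mailers sent to the house and starter foods for its kitchen (section 4.6). Section 2.1 itself points to eating traditions in fire service culture. Some correlation between members of one house is therefore expected, most plausibly for diet.

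The t, Wilcoxon, chi-square and Fisher tests ignore that correlation. A mixed model with a participant effect, or GEE clustered on participant, handles repeated visits by one person but leaves the between-station variance out of the standard error of the treatment contrast. What is at stake is the validity of the central comparison, Group 1 against Group 2, on every outcome. Enrolling more firefighters from the same 44 houses makes the distortion larger.

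**Working it through.** **Is clustering allowed for elsewhere?** The power tables in section 5.2 show how the comparison was conceived. Both checks use individual-level formulas with two-sided alpha 0.05 and no design effect.

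- Body fat, 250 per arm, SD 6.6, difference 1.7: SE = 6.6 × √(2/250) = 0.590. Power = Φ(1.7/0.590 − 1.96) = Φ(0.92) = 82.1%; the protocol states 82%.
- Metabolic syndrome, 18% against 28%, 250 per arm: SE under the null = √(2 × 0.23 × 0.77/250) = 0.0376; SE under the alternative = √((0.18 × 0.82 + 0.28 × 0.72)/250) = 0.0374. Power = Φ((0.10 − 1.96 × 0.0376)/0.0374) = 75.9%; the protocol states 76%.

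Both figures reproduce without any clustering allowance, which agrees with the reading of section 5.1.

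**Size of the understatement.** With k houses per arm, m members per house, between-house variance σ_b² and within-house variance σ_w²:

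- true variance of an arm mean = σ_b²/k + σ_w²/(km)
- variance used by an individual-level test = (σ_b² + σ_w²)/(km)
- ratio = design effect DE = 1 + (m − 1) × ICC

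Inputs: 44 houses (section 1), taken as 22 per arm and of equal size; 500 or 1,000 participants (section 4.3), so m = 500/44 = 11.36 or 1,000/44 = 22.73. The ICC is not in the protocol; 0.01 to 0.05 is assumed, with 0.10 as an upper case for diet.

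True type I error of the naive two-sided 5% test = 2 × [1 − Φ(1.96/√DE)]. The correct interval is wider by √DE.

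| N | ICC | DE | Interval widening | True type I error |
|---|---|---|---|---|
| 500 | 0.01 | 1.10 | 1.05 | 6.2% |
| 500 | 0.02 | 1.21 | 1.10 | 7.4% |
| 500 | 0.05 | 1.52 | 1.23 | 11.2% |
| 500 | 0.10 | 2.04 | 1.43 | 17.0% |
| 1,000 | 0.01 | 1.22 | 1.10 | 7.6% |
| 1,000 | 0.02 | 1.43 | 1.20 | 10.2% |
| 1,000 | 0.05 | 2.09 | 1.44 | 17.5% |
| 1,000 | 0.10 | 3.17 | 1.78 | 27.1% |

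**Check by simulation** (no true effect, 22 against 22 equal houses, 20,000 runs per setting, ICC 0.01 / 0.05 / 0.10). The individual-level t-test rejected in 6.2% / 11.0% / 16.6% of runs with 11 members per house, and in 7.7% / 17.4% / 27.2% with 23. A t-test on the 44 house means rejected in 4.8% to 5.1%.

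**Consequence for power.** Replacing n by n/DE at N = 500 and ICC 0.01 / 0.05 / 0.10 gives 78% / 65% / 52% for body fat and 72% / 58% / 46% for metabolic syndrome. The mMDS example stays above 99%.

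**The case against.** The t-test sentence belongs to a general list of methods and does not name the intervention contrast. The Phase 1 paragraph points to mixed models or GEE, and both families can carry a station effect. The sentence on correlated measurements is not expressly limited to one person, and the protocol nowhere forbids a station term. The section asks only for a brief description, and the exact random-effects structure is ordinarily settled in a SAP.

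These points stand in part. The sponsor may well have intended a station level, and the choice of degrees-of-freedom method is SAP detail. But the protocol does more than stay silent: it names individual-level tests for group differences without restricting their use, and it justifies the longitudinal models solely by repeated measurement of participants. Followed as written, that gives an invalid test of a house-randomised effect at any ICC above zero.

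It is also fair that the error rates apply to an unadjusted comparison at one time point. For a baseline-adjusted longitudinal model the relevant ICC is that of the adjusted outcome, which may differ from the assumed values. At ICC 0.01 and 500 participants the inflation is modest.

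**Conclusion.** The concern holds, and the text needs correcting before analysis. That the analysis plan omits the fire house as a source of correlation is a matter of reading. The size depends on an ICC the protocol does not give: for an unadjusted test, true type I error of about 6% to 17% with 500 participants and 8% to 27% with 1,000, over ICC 0.01 to 0.10. These figures assume 22 equal-sized houses per arm and all participants spread over the 44 houses. The problem would vanish for an outcome only if its ICC were zero, which the house-based delivery makes unlikely.

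**What to change.** Amend section 5.1 so that every between-group comparison accounts for the fire house:

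- Use a mixed model with a random intercept for fire house plus a participant effect for repeated visits, with Kenward-Roger or station-level degrees of freedom (44 − 2 = 42 for Indianapolis). Alternatively, use GEE clustered on fire house with a small-sample sandwich correction.
- Remove the independent t, Wilcoxon, chi-square and Fisher tests as tests of the intervention effect; they may stay for description.
- State how administrative staff are handled. Sections 4.4 and 6.1 place them in Group 1 without a randomised house, so they do not fit the station term and are not part of the randomised contrast.
- As a precaution, state that the station identifier is kept when data are recoded for the statistician (section 15, item r). The protocol does not say that it is removed.
- Restate the power in section 5.2 with an assumed ICC.

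The cost is a few sentences and one model term, with no new data and no change in conduct. Intervals will be wider, and power for body fat and metabolic syndrome will be below the stated figures.
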